The participation should motivate and offer new perspectives of increasing physical activity at the workplace. We have also designed the workshop in such a way that our concept can be used in various companies. In this first step, we want to prove our concept in medium-sized organizations. Due to the current pandemic situation, there is an increasing number of people working in separate offices without any contact with other co-workers. To ensure that these changes do not lead to increased inactivity, new work-related health offers or activity programs should be established. We developed a workshop which takes all the above-mentioned points into account. The use of computer prompts combined with providing information reduces sitting time on average by 14 to 96 min per day*.* In this early stage, we want to prove the concept of our live approach in small groups and hypothesize that the participants show positive health effects (i.e. well-being, decreased MSD) and positive adaptations in their health behavior (i.e. increased physical activity). We hypothesize that additional reminders improve health-related effects. In addition, we want to develop our workshop design in the framework of eHealth applications or a web-based solution, since the integration of such approaches might improve the efficiency of health programs at work [37].

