## Methods

### Participants

We recruit office desk workers aged between 18 and 67 years from different organizations (i.e. public administration with standard office workplaces) in Germany. Two intervention lines are planned: one live workshop group with and one without reminders. After attending the first workshop participants in the appropriate intervention group will receive reminders via e-mail twice a week. The e-mails remind the participants of the possibilities to be physical active at the work place previously introduced through the workshop. Overall, eight e-mails will be sent until participants answer the second online survey one month after participating in the workshop. We use a randomized allocation of the participants to both groups. As inclusion criteria, we define an age group between 18 and 67 years and the employee council of each institution has to approve the participation. Additionally, participants are asked not to take part in other studies during the time of the workshop intervention. Participants are excluded if they take part in only one workshop or do not fill in the questionnaires (missing answers > 30%) appropriately. All participants will be informed about the content and objectives of our study, they can ask questions, and they can withdraw from the participation at any time. As a prerequisite for participation, participants of our study sign a declaration of consent. A meta-analysis [38] revealed small intervention effects of workplace physical activity interventions (d = 0.21). Based on this assumption, power-analysis (G-Power 3.1) indicated in sum 168 participants for an ANOVA with repeated measures (within-between interaction). Our calculation included *f* = 0.11, *α* = 0.05, β = .80, three groups, and three measurements.

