**Fig. 1 Fig1:**
[figure not shown]
Flowchart of the study protocol from contact companies to data analysis (LG = live workshop group). Participants receive a reminder via email

The study lasts about six months for each group. Each workshop and measurement for data collection is promoted by the institutions’ health counselor. Our workshop address three important components for office workers’ health promotion: organizational (i.e. structures, health services), workplace (i.e. equipment, premises), and individual (i.e. health behavior, motivation) components. Details of our intervention are described below. Besides the two interventions groups participants of the control group will receive the pre- and post-study questionnaire.

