### Statistics

All data are processed to enhance quality; for example, in case of missing data, we conduct a missing value analysis (MVA) with a subsequent imputation procedure. Outliers are checked manually. Then, it is planned to perform analyses for repeated measurements of physical wellbeing, HAPA subscales, and the results from the physical activity diary. Results from the Nordic Musculoskeletal Questionnaire are analyzed descriptively. For all analyses, the significance level is set to 0.05.

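### The sample-size paragraph presents 168 participants as giving 80% power on the basis of d = 0.21, but the f = 0.11 entered does not represent that effect in a group-by-time interaction test

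*Protocol article*

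**What the plan says.** The sample-size statement is in Methods, Participants, of the protocol article. It starts from an external effect: "A meta-analysis [38] revealed small intervention effects of workplace physical activity interventions (d = 0.21"). On that basis, "power-analysis (G-Power 3.1) indicated in sum 168 participants for an ANOVA with repeated measures (within-between interaction"). The inputs are listed as "Our calculation included *f* = 0.11, *α* = 0.05, β = .80, three groups, and three measurements". Statistics repeats the alpha: "For all analyses, the significance level is set to 0.05".

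The paragraph does not say how d became f, which correlation between measurements was used, or which pattern of group means over time was assumed.

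Two other statements bear on the calculation. Randomisation is between the two workshop groups ("We use a randomized allocation of the participants to both groups"), and the Introduction has a hypothesis specific to that comparison: "We hypothesize that additional reminders improve health-related effects". The third group is mentioned once, in the text after Fig. 1: "Besides the two interventions groups participants of the control group will receive the pre- and post-study questionnaire".

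**The concern.** In a comparison of two equal groups on one mean, Cohen's f equals d/2. Here d/2 = 0.21/2 = 0.105, which rounds to 0.11, so that conversion appears to have been used. In a within-between interaction, f is something else: the standard deviation of the interaction effects across all group-by-time cells, divided by the within-cell SD. An effect confined to some groups and some time points is diluted when spread over nine cells. The same 0.21 SD then yields a much smaller f, and noncentrality depends on f squared.

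At stake is how the result will be read. Someone who takes the 80% at face value would see a non-significant interaction as fairly strong evidence against an effect of 0.21 SD, when the design would often miss such an effect.

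**Working it through.** **Inputs.** N = 168, f = 0.11, alpha 0.05, k = 3 groups and m = 3 measurements (Participants). The printed β = .80 is read as power 0.80, which the reproduction below confirms. Assumed here: correlation ρ as shown, sphericity (ε = 1), equal groups (the ratio is not stated), no dropout and no clustering.

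**1. Reproducing 168.** The G*Power default for this test uses λ = N·f²·m/(1−ρ), df1 = (k−1)(m−1), df2 = (N−k)(m−1).

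- With ρ = 0.5: λ = 168 × 0.0121 × 3/0.5 = 12.20, df = 4 and 330, power 80.3%. The smallest N in equal groups is 168.
- Other correlations give other sizes: 333 (ρ = 0), 234 (0.3), 102 (0.7). The alternative effect-size options in the software give 501 and 498.
- Of the settings tried, only ρ = 0.5 with the default option gives 168 for three groups and three measurements.

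**2. Rounding alone.** With f = 0.105, λ = 168 × 0.011025 × 6 = 11.11 and power is 76%. The required N would be 183.

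**3. The f that 0.21 SD produces.** If the mean difference is d × (group pattern) × (time pattern), then f = SD(group pattern) × SD(time pattern) × d, using population SDs.

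- A: both workshop arms gain d at both follow-ups. Group (1, 1, 0) and time (0, 1, 1) each have SD 0.471, so f = 0.471 × 0.471 × 0.21 = (2/9) × 0.21 = 0.047. A gain in one arm only gives the same f.
- B: as A, but building linearly, time (0, 0.5, 1), SD 0.408. f = 0.471 × 0.408 × 0.21 = 0.040.
- C: workshop 0.21, workshop plus reminders 0.42, at both follow-ups. Group (0, 1, 2), SD 0.816. f = 0.816 × 0.471 × 0.21 = 0.081.

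For A at ρ = 0.5, λ = 168 × 0.00218 × 6 = 2.20.

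| Power at N = 168 | ρ = 0.5 | 0.7 | 0.8 | 0.9 |
|---|---|---|---|---|
| A (f = 0.047) | 18% | 29% | 43% | 75% |
| B (f = 0.040) | 15% | 22% | 32% | 61% |
| C (f = 0.081) | 51% | 75% | 92% | >99% |

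A simulation of pattern A (4,000 runs per correlation) gave 19%, 29% and 43% at ρ = 0.5, 0.7 and 0.8. If the control group has only two measurements, as the text after Fig. 1 suggests, a 3 × 2 version of A gives 19% at ρ = 0.5.

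**4. What f = 0.11 implies.** Pattern A: 0.11/(2/9) = 0.50 SD. Pattern B: 0.11/(0.471 × 0.408) = 0.57 SD. Pattern C: steps of 0.11/(0.816 × 0.471) = 0.29 SD. Reaching 80% power under A with d = 0.21 takes 918 participants at ρ = 0.5, 552 at 0.7 and 369 at 0.8.

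**5. The reminder contrast.** The protocol gives no effect size for it. As an illustration, assume 0.21 SD at one follow-up, r = 0.5, two-sided 0.05. The SD is √(2(1−0.5)) = 1 for change and √(1−0.25) = 0.866 with baseline adjustment. Arms of 56 correspond to 168/3, arms of 84 to 168/2.

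| Per arm | Power, change | Power, adjusted | Detectable at 80%, change | Detectable at 80%, adjusted |
|---|---|---|---|---|
| 56 | 20% | 25% | 0.534 SD | 0.463 SD |
| 84 | 27% | 35% | 0.435 SD | 0.377 SD |

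**The case against.** The strongest reply is that no single low power figure can replace the 80%. It depends on correlation, pattern and test. The Introduction expects both a workshop benefit and an added reminder benefit. Pattern C combines the two and reaches 92% at ρ = 0.8. For the reminder contrast, a baseline-adjusted analysis of the mean of both follow-ups would give 34% (56 per arm) or 48% (84 per arm) at r = 0.5, more than a single follow-up gives. This stands, and a reader should not conclude that the true power is simply 20–35%. It does not rescue the printed claim: pattern C assumes twice the cited effect in one arm, and ρ = 0.5 is the value that yields 168. At that value C gives 51%.

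A reader might also infer that the protocol promises 80% power for reminders versus no reminders. It does not. The calculation is tied to the three-group interaction, and the cited d to workplace physical activity interventions in general. The 0.21 SD for reminders in the working is an assumption made here.

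The d/2 origin of f is likewise an inference. The numbers fit and no other derivation is offered, but the text does not say it. The conclusion does not need it: f = 0.11 fails to match 0.21 SD under A and B however it was obtained.

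Finally, one might want the interaction test replaced by a single contrast at one time point. The documents do not force that. Statistics names no confirmatory test, the choice may be settled in an analysis plan not shown, and the replacement would leave the workshop-versus-control hypothesis without a test.

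**Conclusion.** The point holds. The arithmetic from f = 0.11 to 168 is right at ρ = 0.5, but the step from d = 0.21 to f = 0.11 is not. For a 0.21 SD gain in the stated 3 × 3 interaction, power at 168 is 15–18% at ρ = 0.5. For the sustained gain (pattern A) it stays below 80% even at ρ = 0.9 (75%). The printed 80% corresponds to roughly 0.50–0.57 SD under patterns A and B, more than twice the cited effect. Only a larger assumption than the one cited brings power near or above 80%, and then only at correlations above the 0.5 that 168 implies.

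These figures assume equal groups, sphericity, no dropout and no clustering. Participants plans exclusions and the workshops run in small groups. Allowing for either would generally lower power further.

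**What to change.** Keep 168 and correct the sample-size paragraph:

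- State the correlation and the assumed pattern of group means over time.
- Delete the claim of 80% power for d = 0.21, and relabel β = .80 as power.
- Give the power by correlation and pattern, or the detectable difference. At r = 0.5 and 80% power, the latter is a two-arm difference of 0.534 SD in change or 0.463 SD baseline-adjusted with 56 per arm, and 0.435 or 0.377 SD with 84 per arm. Say which group sizes apply.

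In Statistics, add that the reminders versus no-reminders contrast, the randomised comparison, is reported with its confidence interval alongside the planned interaction test. The 4-df omnibus test can be significant through workshop-control differences alone, so it does not answer the reminder question by itself.

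The cost is a less favourable stated power and one added contrast. No extra participants are needed, and Data Availability says the study has not started.

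### The 168 participants and 80% power belong to a three-group interaction test, not to the randomised comparison of workshop with and without reminders

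*Protocol article*

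**What the plan says.** All references are to the protocol article.

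- **Hypotheses (Introduction).** The authors "hypothesize that the participants show positive health effects (i.e. well-being, decreased MSD) and positive adaptations in their health behavior". The second hypothesis concerns the reminders: "We hypothesize that additional reminders improve health-related effects".
- **Randomisation (Abstract, Methods; Participants).** Random allocation is described between two groups only, workshop with reminders and workshop without.
- **Sample size (Participants).** The starting point is a meta-analysis showing "small intervention effects of workplace physical activity interventions (d = 0.21"). The calculation "indicated in sum 168 participants for an ANOVA with repeated measures (within-between interaction"). Its inputs are given as "Our calculation included *f* = 0.11, *α* = 0.05" and "β = .80, three groups, and three measurements". The .80 is printed as β but is evidently the power.
- **Control group (Study-aim and procedure).** A control group appears here, with questionnaires before and after the study only. It is not mentioned in the description of the randomisation.
- **Analysis (Statistics).** "it is planned to perform analyses for repeated measurements of physical wellbeing, HAPA subscales, and the results from the physical activity diary", at a significance level of 0.05. This section does not single out a group comparison.

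**The concern.** The reminder question involves two arms and has a direction. The interaction used for the sample size has (3 − 1) × (3 − 1) = 4 degrees of freedom, and its null says that control, workshop, and workshop plus reminders all change over time in the same way. If the workshop beats control, that null is false even when the two workshop arms are identical. The rejection is then correct for the test's own null but gives no information about reminders. It would also rest on a group that is not described as randomised.

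The stated 80% is at stake too. A reader will take it as the chance of detecting what the trial randomises. If that chance is much lower at the cited d = 0.21, a null result on reminders would be over-interpreted.

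**Working it through.** **Inputs from the Participants section:** N = 168, f = 0.11, α = 0.05, power 0.80, k = 3 groups, m = 3 measurements, source effect d = 0.21 (d/2 = 0.105, so f = 0.11 is this rounded up).

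**Assumptions, not stated in the article:** correlation ρ = 0.5 between measurements, sphericity, SD = 1, and equal groups of 168/3 = 56.

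**1. Reproducing the plan's figure.** For the within-between interaction, λ = f² × N × m / (1 − ρ) = 0.0121 × 168 × 3 / 0.5 = 12.2. The degrees of freedom are 4 and (168 − 3) × 2 = 330. The noncentral F gives power 0.803, and 168 is the smallest balanced N reaching 0.80. The arithmetic is sound, and it confirms which test the 168 belongs to.

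**2. The same test when only one component works.** Let the effect d be present at both follow-ups.

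- Workshop works, reminders add nothing: the group pattern is (0, d, d).
- Only reminders work: the group pattern is (0, 0, d).

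In either case the interaction sum of squares per participant is d² × (2/3) × (2/3) = 4d²/9, so λ = 56 × (4/9) × d² / 0.5.

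| d | λ | Rejection rate, either case |
|---|---|---|
| 0.21 | 2.20 | 18% |
| 0.30 | 4.48 | 35% |
| 0.40 | 7.96 | 60% |
| 0.50 | 12.44 | 81% |

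The test cannot tell the two cases apart. Simulation with 5,000 trials per scenario agreed within about 1 point: at d = 0.21 it gave 18.8% (workshop only) and 18.0% (reminders only), and with no effect anywhere 5.2%. At ρ = 0.7 the rate at d = 0.21 is 29%.

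The implied f is √(4d²/81) = 0.222d, so f = 0.11 corresponds to d of about 0.50 here. With a linearly growing effect the corresponding d is about 0.58, and the rate at d = 0.21 is 15%.

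**3. Both components work.** If the workshop and the reminders each add 0.21, the pattern is (0, 0.21, 0.42) and λ = 56 × 2 × 0.21² × (2/3) / 0.5 = 6.59. The rejection rate is about 50%, or 39% with linear growth. This is below 80%, and the result would not show which component produced it.

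**4. The direct two-arm comparison.** Baseline-adjusted, 56 per arm, two-sided 0.05, ρ = 0.5, d = 0.21.

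- One follow-up: residual variance 1 − 0.5² = 0.75; standard error √(2 × 0.75 / 56) = 0.164; noncentrality 0.21 / 0.164 = 1.28; power 25%.
- Mean of both follow-ups, effect sustained: residual variance 0.75 − 0.25 = 0.50; standard error 0.134; noncentrality 1.57; power 34%.
- At ρ = 0.7 these become 34% and 45%.
- If all 168 were in the two arms (84 each), at ρ = 0.5: 35% and 48%.
- For 80% power at ρ = 0.5: about 268 and 179 per arm.

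**5. A short-lived reminder effect.** If reminders act only at the first follow-up, averaging halves the effect. At d = 0.21 / 0.3 / 0.4 the averaged comparison has 12% / 20% / 32%, and the three-group interaction 18% / 35% / 60%. A comparison at that follow-up alone has 25% / 44% / 68%.

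**The case against.** The strongest case on the other side has five parts.

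- **No decision rule is stated.** A reader might infer that a significant interaction will be reported as a reminder effect. The article does not say so. It names the test only as the basis of the sample size, and follow-up contrasts may be in an analysis plan that is not shown. This stands: the missing contrast in the Statistics section is not the fault. But a contrast added later does not turn the published 80% into the power of that contrast.
- **The high rejection rates need large effects.** A reader might infer that the test will usually be significant when reminders do nothing. At d = 0.21 the rate is 15% to 18% at ρ = 0.5. The 60% and 81% need a workshop effect of 0.4 to 0.5, about twice the cited one, and with no effect in any group the test holds 5%. This stands.
- **The control group may not be able to drive the test.** It has two questionnaires, not three measurements, so the test cannot be run as powered. This stands. It is a further reason to reconcile the sections, not a defence of the calculation.
- **The direct comparison gains less than it may seem.** Without baseline adjustment, a one-degree-of-freedom contrast on mean change has 25% / 44% / 68% at d = 0.21 / 0.3 / 0.4, only 6 to 9 points above the interaction. Much of the 16 to 25 point gain of the adjusted, averaged contrast comes from the adjustment. This stands.
- **Averaging the follow-ups can be worse.** The eight e-mails end at the second survey, and the Introduction cites short-term effects of text messages. Step 5 shows the loss, so no averaged endpoint is prescribed here.

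**Conclusion.** The concern holds as a mismatch between the powered test and the randomised question. The sample-size arithmetic is correct for the test named, but that test's null is not that reminders add nothing, and rejecting it does not by itself support a reminder effect. At the plan's own d = 0.21 it rejects in about 18% of trials, whether only the workshop or only the reminders work. The 80% is reached only near d = 0.5. A direct comparison of the two randomised arms has about 25% to 34% power at d = 0.21.

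These figures rest on 56 per group, ρ = 0.5 and, except for the single-follow-up comparison, an effect sustained at both follow-ups. At ρ = 0.7 they rise to 29% for the interaction and 34% to 45% for the direct comparison, which leaves the conclusion unchanged.

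**What to change.** 1. In Participants and Statistics, name a baseline-adjusted comparison of workshop with reminders against workshop without as the test of the reminder hypothesis. Choose one follow-up, or one summary of the follow-ups, in advance to match when reminders are expected to act.
2. Restate the power in Participants for that comparison, with the assumed correlation and arm sizes: about 25% (single follow-up) to 34% (mean of two sustained follow-ups) at d = 0.21 with 56 per arm and ρ = 0.5. Then justify the sample size on that basis.
3. Report workshop against control separately, on the pre-post questionnaires, labelled non-randomised unless the allocation of the control group is clarified. Treat the three-group interaction as descriptive.
4. Reconcile the "three groups, and three measurements" of the power analysis with the control group's two questionnaires in Study-aim and procedure.

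**Cost.** The article states that the study has not started, so these are wording changes that need no new data. The restated power is much less favourable than 80%. Reaching 80% at d = 0.21 would need about 179 to 268 per arm at ρ = 0.5. Fixing one time point gives up sensitivity at the other, and averaging gives up sensitivity to a short-lived effect.

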### Study-aim and procedure

Our study aims to examine health-related effects from two slightly different live workshops with office workers. Therefore, we contact health counselors at various companies in Germany. If they are interested in participating in our study, further details will be discussed and the employee council and management level will be involved. If the management approves our study, the health counselors will be interviewed and will help to distribute the information among the employees (i.e. via email). In an email, participation in one of our groups will be clearly explained. The study information and the consent form are attached to this email, with additional contact details of the study supervisors (i.e. regarding upcoming questions). As a prerequisite for participation, these documents must be signed and returned. The participants have the opportunity to choose a suitable date from a list of workshop dates in their company. Each participant receives a link to participate in the online questionnaire as well as an activity diary one week before their first workshop. Additionally, we use accelerometers to objectively measure physical activity during this week. Accelerometers with instructions, activity diaries and an online survey will be sent to all consenting participants for data collection. The instructions explain how to attach the accelerometer to the participant’s thigh and hip. Previous studies have indicated three days are sufficient to observe a stable pattern of physical activity [39]. Not wearing the accelerometer for 3 successive days leads to exclusion of the participant from the study.

This procedure is repeated one week before the refresher workshop and after six months. We have no blinding of our workshop supervisors and outcome assessors or data analysts. In each group data collection starts one week before the first workshop. The study procedure is presented in Fig. 1.

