**Methods:**

We use a randomized controlled trial with two intervention groups: a live workshop with and without additional reminders. The workshop intervention design consists of a baseline measurement, two workshops, and one follow-up measurement. Each workshop takes place in small groups (*n* < 11). We use a randomized allocation to both groups. To control for health-related effects and the expected behavior change we examine (i) physical activity (i.e. active time, taken steps, etc.) by a tracking device (ii) physical wellbeing, motivation, and volition by an online questionnaire, and (iii) participants also report physical activity by a diary. All measurements are taken one week before the respective workshop and 24 weeks after the initial baseline measures.

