#### Nordic musculoskeletal questionnaire (NMQ)

This questionnaire aims to detect musculoskeletal stress in different regions of the body [40]. The NMQ consists of two parts: first, general information about the participant including the individual situation at work, and second, detailed questions about previous and existing physical stress. The latter also examines special regions of the body (i.e. neck, shoulder, lower back). All questions include the duration and frequency of physical stress, especially during the last 12 months and the last seven days. Previous research concluded that the NMQ is sensitive, repeatable, and a useful screening tool [41]. We use this questionnaire in two ways: (i) as a screening tool to adapt the physical activities in our refresher-workshop, and (ii) to record changes in physical stress a few weeks after the workshop.

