## Discussion

We introduced a workshop to increase health-seeking behaviors in office workplaces in Germany. Our workshop is based on a combination of physical activity and health behavior planning.

At first, we want to indicate one minor limitation regarding our data acquisition: we have to validate our PAD. The diary is adapted to a validated questionnaire; however, that questionnaire has not been validated for daily usage. Moreover, the literature showed differences between self-reported (i.e. by questionnaires) and accelerometer-measured physical activity [48, 49]. Therefore, we use accelerometer-measured physical activity to prove our PAD in a sub-sample of our participants. If the result of our analysis shows insufficient validity, only the data from the accelerometry will be used. Another limitation refers to the recruitment process. The participants are recruited in different organizations and therefore have different pre-conditions (i.e. workplace equipment, health services) as well as differently effective health counsellors. Thus, we will collect data on the organization to control for potential experimenter effects between organizations.

In addition, there is some risk of inter-subject group bias if individuals in one group inform a member of the other group about reminders. In the follow-up survey, we will ask the group without reminders whether they received information about the procedure in the other group. We can then perform analyses according to whether participants received information about the other group and exclude them from the analyses, where necessary. Participants of the workshops might be less active in winter. Hence, the season could affect the amount of physical activity. As data of both intervention groups will be collected in the same season, they remain comparable. All these issues could affect our results and should be critically reviewed later.

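### Workshop participants are grouped in sessions of at most 10 within companies, but neither the sample size of 168 nor the stated analyses allow for correlation within sessions

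*Protocol article*

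**What the plan says.** The abstract of the protocol article states: "Each workshop takes place in small groups", with a limit of fewer than 11. Under Study-aim and procedure, session membership is self-chosen within the employer: "The participants have the opportunity to choose a suitable date from a list of workshop dates in their company". Sessions are therefore nested in companies.

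Several elements are shared:
- Table 1, part IV, has the group exchange experiences and work on action plans before each person writes an individual plan.
- Under Measurements, small discussion parts are adapted to the company.
- The NMQ serves "as a screening tool to adapt the physical activities in our refresher-workshop".

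The sample size is given under Participants: "power-analysis (G-Power 3.1) indicated in sum 168 participants for an ANOVA with repeated measures (within-between interaction"). Its inputs are: "Our calculation included *f* = 0.11, *α* = 0.05, β = .80, three groups, and three measurements". No ICC or design effect is listed. The Statistics section plans analyses for repeated measurements and names neither session nor company. The Discussion adds: "Thus, we will collect data on the organization to control for potential experimenter effects between organizations". It gives no method and does not mention sessions.

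Participants are described as allocated at random to the two workshop groups. The text does not say whether one session can contain both groups. The control group is described only as receiving questionnaires, so it attends no sessions.

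**The concern.** People who sit in the same small session share trainers, discussion and group planning. They also choose that session themselves, alongside colleagues. Their changes over time are likely to be correlated, so a session of 10 carries less information than 10 unrelated people.

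The effect of ignoring this differs by contrast:
- **Workshop versus control:** only the workshop side is clustered, and its standard error is understated.
- **Before-after change among workshop participants:** the standard error is understated in full.
- **Reminder versus no reminder:** it is understated if each session belongs to one arm. If arms are mixed within sessions, the shared session effect cancels from the contrast, and ignoring it costs some precision.

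At stake are false-positive rates above 5% for the affected tests and a power below the one claimed.

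**Working it through.** **1. The plan's own figure.** From the Participants section: f = 0.11, α = 0.05, three groups (k = 3), three measurements (m = 3), and the printed β of .80 read as power. Two inputs are not printed and are assumed here: correlation between measurements ρ = 0.5, and sphericity (ε = 1).

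For the within-between interaction:
- λ = f² × N × m / (1 − ρ)
- df1 = (k − 1)(m − 1)
- df2 = (N − k)(m − 1)

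At N = 168, λ = 0.0121 × 168 × 3 / 0.5 = 12.20, df1 = 4, df2 = 330, and power is 0.803. The smallest N reaching 0.80 is 167, which becomes 168 for three equal groups. The figure is reproduced with independent participants, so it contains no allowance for clustering.

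**2. Design effect.** DE = 1 + (c − 1) × ICC, where c is session size. The powered test concerns change over time, so the ICC meant is that of change. The documents give none; 0.01 to 0.10 is an assumed range. The largest session the abstract allows is 10; 5 is shown as a smaller case.

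**3. Power at 168.** Assume 56 per arm and unclustered controls. Effective N is approximately 56 + 112/DE, which is put into the formula of step 1.

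| c | ICC | DE | Effective N | Power |
|---|---|---|---|---|
| 10 | 0.01 | 1.09 | 56 + 102.8 = 158.8 | 78% |
| 10 | 0.05 | 1.45 | 56 + 77.2 = 133.2 | 69% |
| 10 | 0.10 | 1.90 | 56 + 58.9 = 114.9 | 62% |
| 5 | 0.01 | 1.04 | 56 + 107.7 = 163.7 | 79% |
| 5 | 0.05 | 1.20 | 56 + 93.3 = 149.3 | 75% |
| 5 | 0.10 | 1.40 | 56 + 80.0 = 136.0 | 70% |

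This treats each workshop arm as clustered in its own sessions. With mixed sessions the loss falls only on the comparison with control, so it is smaller.

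**4. Type I error of a naive 5% test, sessions of 10.** The error is 2 × (1 − Φ(1.96/√R)), where R is true variance over naive variance.

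| Contrast | R | ICC 0.01 | ICC 0.05 | ICC 0.10 |
|---|---|---|---|---|
| One workshop arm vs control | (DE + 1)/2 = 1.045 / 1.225 / 1.45 | 5.5% | 7.7% | 10.4% |
| Both workshop arms pooled vs control | (DE + 2)/3 = 1.03 / 1.15 / 1.30 | 5.3% | 6.8% | 8.6% |
| Reminder vs none, whole sessions in one arm | DE = 1.09 / 1.45 / 1.90 | 6.0% | 10.4% | 15.5% |
| Reminder vs none, arms mixed in sessions (simulated) | below 1 | 4.8% | 4.3% | 4.1% |

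The simulation used 12 sessions of 10, a t-test on change scores and 20,000 runs. For whole sessions in one arm it gave 6.3% / 10.4% / 16.2%, in line with the formula. A pooled before-after test has R = DE and so the same formula values as the third row.

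**The case against.** A reader might infer that error bars are too narrow throughout. The documents do not support that. Allocation is of participants, the arms differ only by e-mails sent after the first workshop, and the Discussion worries that one group may tell the other about reminders. Mixed sessions are therefore quite possible. In that case the naive reminder contrast, the comparison the abstract describes as randomised, is slightly conservative. This objection stands, and it confines the concern to the contrasts named above.

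It is also tempting to divide all 168 by the design effect for sessions of 10, which gives power of 76% / 62% / 49%. That would cluster controls who attend no session and would use only the maximum session size. Stable differences between companies, and similarity of colleagues at baseline, largely cancel from change scores, so the relevant ICC may be small.

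The Statistics section does not fix an ANOVA, which is named only in the power calculation. A mixed model would fit its wording, and its random effects may stand in a fuller plan. The shared content should not be overstated either: only small discussion parts follow the company, the NMQ adaptation is not said to be made per session, and each participant ends with an individual plan. Finally, the Discussion does recognise differences between organisations.

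None of this puts clustering into the published 168. A later analysis plan could add a session effect, but the power at that number would still be lower than claimed if the ICC is above zero.

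**Conclusion.** The point holds in limited form. With the printed inputs, 168 is the independent-observations figure, and no stated analysis handles sessions. Standard errors that ignore session are too small for workshop versus control and for pooled before-after change. They are too small for the reminder contrast only if whole sessions belong to one arm.

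Over the assumed ICC range the power loss runs from about one point (sessions of 5, ICC 0.01) to about 18 points (sessions of 10, ICC 0.10). With sessions of 10, naive type I error for one workshop arm versus control runs from 5.5% to 10.4%. These sizes rest on an ICC the documents do not give, equal arms of 56, unclustered controls, ρ = 0.5 and sphericity. The direction for the two always-affected contrasts needs only a positive ICC of change. The matter should be corrected, and the Data Availability statement says the study has not yet started.

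**What to change.** 1. Analyse all repeated outcomes with a linear mixed model: random intercepts for participants, a random session effect on change (partially nested, each control as a singleton) and company as stratum. With 112 workshop participants in sessions of 10 there would be only about 11 sessions (112/10 = 11.2), so use small-sample degrees of freedom.
2. Record a session identifier for every workshop participant.
3. State whether a session may contain both arms. Preferably randomise individuals within company after dates have been chosen, so that date choice cannot determine the arm and the reminder contrast is made largely within sessions.
4. Replace the single 80% claim by power over a range of ICC and session size. If 80% is to be kept with sessions of 10, simple inflation of the workshop arms (56 + 112 × DE, rounded up) gives 179 / 219 / 269 for ICC 0.01 / 0.05 / 0.10.

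The cost is one added variable, revised analysis wording and a small change to the order of date choice and allocation. The intervals for the affected contrasts will be wider and the stated power lower.
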